### Non-inferiority margin

In non-inferiority trials, the choice for a specific non-inferiority margin (NI margin) is critical for the interpretability of the study. This choice can be based on prior art (use of NI margin in comparable studies), expert opinion or data-driven, based on association with other (un)intended effects. We have found three non-inferiority studies that have used the DAS28 as a primary outcome measure. All three studies have chosen to use a NI margin of 0.6. [23–25]. Although no clear explanation is given by the authors regarding the rationale for this NI margin, a non-inferiority margin of 0.6 points in DAS28 seems a reasonable choice, as the error of measurement in DAS28 is 0.6 [26]. This error of measurement is used in the EULAR response criteria to denote the difference between a non-response and a moderate response in DAS28 [27]. Regarding assay sensitivity, the mean difference between placebo and RTX, added to MTX, in DAS28, is 1.2 according to a recent meta-analysis [1]. This means that the NI margin of 0.6 is sufficiently smaller than the treatment effect of RTX against placebo. We have therefore chosen to use this NI margin of 0.6, although it always remains debatable what an acceptable small NI margin is. This is especially important to prevent a situation where multiple non-inferiority studies are performed after each other, each using the non-inferior treatment from the last study as a comparator for a new treatment. In this context, although treatment B is non-inferior to A, and C is non-inferior to B, treatment C can in fact be inferior to A, the so called biocreep [28].

### Assay sensitivity

Since this is a non-inferiority trial, assay sensitivity – the ability to demonstrate inferiority with the chosen trial design – is an important issue. Assay sensitivity could be established by a placebo arm showing that not retreating with RTX is inferior to retreating with RTX. Considering it has been shown in earlier studies that the mean disease activity of patients will increase when not retreated with RTX [29], it seems unnecessary and unethical to include a placebo arm. Therefore, the comparator is a standard low-dose of RTX, while the group sizes should be large enough to gain a sufficient level of precision (see sample size calculation).

### Patients

Inclusion criteria for patients in this pragmatic study are as non-restrictive as possible. This is based on the underlying principle that the results of this trial should be generalisable to all RA patients who are doing well on their RTX treatment. We therefore include RA patients fulfilling either 2010 EULAR/ACR RA [30] and/or 1987 RA [31] criteria and/or having a clinical diagnosis of RA according to the treating rheumatologist, at any time point between start of the disease and inclusion.

Patients are eligible if they were treated at least once with regular low-dose RTX treatment in the last 18 months for RA, so in a dose of 1 × 1000 mg, 2 × 1000 mg or 2 × 500 mg, and had received no other bDMARDs after the last RTX dose. Patients treated with innovator RTX (MabThera®) as well as authorised RTX biosimilars in similar doses as conventional RTX will also be included.

It is somewhat difficult to operationalise the criterion that patients need to be doing well enough on RTX because of the variety of retreatment strategies that are used in clinical practice. We decided on at least six months of stable, low-disease activity after the last RTX infusion (operationalised by either DAS28-CRP < 2.9/DAS28-ESR < 3.2 or judgement of low-disease activity by a rheumatologist) and a current DAS28-CRP ≤ 3.5/DAS28-ESR ≤ 3.8. The latter criterion is added, because patients are often not retreated at fixed intervals, but are retreated either based on treat-to-target or on demand when disease activity increases. However, we do not want to generalise to patients being treated only when they flare severely, as it has been shown that the optimal strategy for RTX retreatment (although not completely clear yet) is either fixed interval or treat-to-target, but not treated only on demand. Also, a high SD in disease activity at study start would increase the required sample size.

Further inclusion criteria are chosen to ensure that we are able to study the participants and to measure the outcomes: patient informed consent; age ≥ 18 years and mentally competent; life expectancy > 6 months; no planned relocation out of reach of study centre; and able to read and communicate well in Dutch.

For generalisability reasons, exclusion criteria are kept minimal and only exclude patients with known (non-) response to ultra-low-dose RTX (below 1 × 1000 mg), to prevent selection bias, and current corticosteroid dosing above 10 mg per day prednisolone equivalent, because these patients should preferably first taper their corticosteroid.

### Patient recruitment

All eligible patients will be selected and approached based on information from the electronic health record according to the abovementioned inclusion and exclusion criteria. Patients will be asked to join this study by their treating rheumatologist using a letter accompanied with the patient information (including the informed consent form). Informed consent is obtained before patients receive the study medication and baseline data are collected.

### Randomisation and blinding

Participants will be allocated to the treatment groups at a ratio of 1:2:2 (1 × 1000 mg vs. 1 × 500 mg vs. 1 × 200 mg). The experimental groups are larger than the control group to increase experience with the lower dosing and with the additional benefit that a larger number of potential predictive factors for response can be studies in multivariate prediction modelling in the ultra-low-dose RTX groups.

Randomisation will be performed using a computerised randomisation procedure and stratified to ensure equal distributions of two possible effect modifiers for response to ultra-low-dose RTX, concomitant conventional DMARD use and RF/ACPA status. Patients will be randomised using block randomisation in variable block sizes (multiples of 5) to more closely achieve the intended allocation ratio and to ensure that the allocation of participants will not be predictable. Patients, physicians, nurses, researchers and data analyst/statistician will be blinded for treatment allocation. The allocation is kept in opaque, sequentially numbered envelopes; envelopes are sequentially assigned by the pharmacist to each next patient. The infusions for the study will be prepared by the hospital pharmacy based on the randomisation number, the physical appearance of the three interventions will be indiscriminate (see below). Unblinding is expected to be rarely necessary (all patients receive RTX and retreatment with 1000 mg is allowed when necessary), but is possible after consulting the coordinating centres pharmacist.

### Interventions

Patients allocated to the standard low-dose group will receive a (blinded) single 1000 mg RTX infusion according to the standard protocol for infusion of rituximab. Patients allocated to the ultra-low-dose groups will receive 500 mg or 200 mg. This dose will be diluted to the same volume as the standard low-dose infusion to ensure the blinding of the study, all premedication and procedures are identical to the standard low dose. Of note, the possible advantage of shorter infusion times cannot be assessed in our study, because this would lead to patients and healthcare providers being unblinded.

It is aimed to leave all other rheumatic treatment unaltered as much as possible during the study period. However, all treatment decisions are left to the discretion of the treating physician and (changes in) use of paracetamol (acetaminophen), tramadol, non-steroidal anti-inflammatory drugs (NSAIDs), oral corticosteroids and DMARDs are all allowed during this study to ensure good care. During each visit, patients are asked about the use of these medications. Suggested treatment in case of clear loss of response is escape treatment with an extra dose of 1 × 1000 mg RTX. This can be done without unblinding, since the authorised dose of RTX is 2 × 1000 mg per six months and no patients will exceed this dose as the maximum study dose is 1 × 1000 mg.

We have determined several medication changes that are defined as ‘treatment failure’. These changes are: receiving an extra dose of RTX within the six-month study period; receiving another bDMARD (thus switching to another type of bDMARD); and using corticosteroids in a dose > 10 mg/day. Starting a concomitant conventional synthetic (cs)DMARD during the study period is not considered a treatment failure. The reasoning behind this is that all included patients will have received these csDMARDs before, with little effect on their RA, and the concomitant csDMARD is generally given as an adjuvant to increase the effectiveness of RTX.

In case of treatment failure, the patients will remain in the study, but the last measure of disease activity and other outcomes will be used as outcome employing a ‘last observation carried forward’ strategy.

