#### Assessments

At baseline, several characteristics of the patients will be measured, including demographics, disease and treatment characteristics. Also, possible predictors for response to ultra-low-dose RTX from peripheral blood will be collected, including (anti-)RTX drug levels and peripheral CD19 counts. Thereafter, visits will be performed at three and six months and when necessary in between (Fig. 1).

Several measures on disease activity will be collected during the study. The DAS28-CRP is a validated and widely accepted measure for RA disease activity and will be used as a primary outcome measure. It consists of four components: 28 tender joint count; 28 swollen joint count; CRP (mg/L); and patients VAS assessment of global disease activity (0–100) [26]. Remission is defined as DAS28-CRP < 2.4 and low disease activity by DAS28-CRP < 2.9 [32]. In addition, patient VAS assessment of pain, rheumatologist VAS assessment of global disease activity, acute phase reactants (CRP and ESR) and the OMERACT patient flare questionnaire are collected. To measure functioning of patients, the HAQ-DI, a validated instrument that is widely used in rheumatology is applied [33]. Quality of life is assessed using EQ5D-5 L, which is a validated instrument and comprises five questions and a visual analogue self-rating scale [34].

Adverse events are assessed at every visit during the study period and classified according to the Common Toxicity Criteria (CTC) [35]. In addition, we focus explicitly on infusion reactions and infectious events. Patients are asked to complete a short questionnaire after the RTX infusion on the occurrence of infusion-related adverse events. Medication use is charted using data from the electronic patient records on the use of DMARDs, corticosteroids and NSAIDs.

Costs will be calculated from a societal perspective. We will include the cost of outpatients’ clinic visits and telephone consultations, travel expenses for patients, costs of hospitalisation due to RA, costs due to health-related work absence and costs of medication during the six-month study period.

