**Table 1 Tab1:** Total trial sample size at various correlations between endpoints

SD change	r	Sample size 1000 mg arm	Total trial size (5 x sample size in 1000 mg arm)
0.9	0.17	26	130
0.8	0.35	24	120
0.7	0.5	20	100
0.6	0.63	16	80

To protect for a too optimistic correlation, we therefore choose a total trial size of 130 and this is further increased to 140 patients to account for patient drop-out.

Primary analyses will be done per protocol (PP), as this is the most conservative approach for a non-inferiority study. In addition, analyses will be performed on an intention-to-treat basis (ITT). For PP analysis, we will include patients who have received the study medication and completed follow-up of six months or until treatment failure (and last observation of disease activity carried forward).

The primary endpoints will be tested using 95% confidence intervals based on linear regression with the change in DAS28-CRP as outcome, dose group as determinant and baseline values of DAS28-CRP as covariate (ANCOVA).

To find predictors (including age, sex, disease duration, RF/ACPA status, CD19+ B-cell count, serum RTX, serum anti-RTX), patients will be categorised into responders (DAS28-CRP < 2.9 at six months and no treatment failure) and non-responders (all other patients). The absolute number (and thus also proportion) of responders will determine the number of predictors that is admissible for analysis, according to the rule of ten-events-per-variable given that predictors are predetermined. Univariate logistic regression analysis will be performed for the admissible predictive factors, with a deliberately liberal *p* < 0.20 as selection criterion. Univariately significant variables are entered in a full multivariate logistic regression model, that is step-wise reduced until all *p* < 0.20. Internal validation and shrinkage will be performed using a bootstrapping procedure with 1000 repetitions. Performance of the multivariate predictive model will be evaluated using discrimination (area under the receiver operator curve) and calibration (calibration slope, calibration plot and Hosmer-Lemeshow test).

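### Carrying forward the last DAS28-CRP after treatment failure can score a failed patient with a pre-flare value, because the carried-forward measurement is not tied to the failure

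*Protocol article*

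**What the plan says.** The Interventions section of the protocol article defines failure by medication. One of its three criteria is "receiving an extra dose of RTX within the six-month study period"; the others are a switch to another bDMARD and corticosteroids above 10 mg/day. On rescue it says: "Suggested treatment in case of clear loss of response is escape treatment with an extra dose of 1 × 1000 mg RTX". Patients who fail stay in the study, but "the last measure of disease activity and other outcomes will be used as outcome employing a" last-observation-carried-forward strategy.

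The section Sample size considerations and statistical analyses places the rule in the primary analysis. The per-protocol set contains treated patients who "completed follow-up of six months or until treatment failure (and last observation of disease activity carried forward". On the choice of that set it says: "Primary analyses will be done per protocol (PP), as this is the most conservative approach for a non-inferiority study". The estimator is "linear regression with the change in DAS28-CRP as outcome, dose group as determinant and baseline values of DAS28-CRP as covariate (ANCOVA", and the margin is 0.6.

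Under Assessments, "visits will be performed at three and six months and when necessary in between". The text does not say that DAS28-CRP is measured when a patient fails, or that such a value is the one carried forward.

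**The concern.** Failure is triggered by a prescription, not by a DAS28-CRP. Treatment decisions are left to the physician, and medication use is charted from electronic patient records. A failure can therefore be on record with no joint count or CRP from the same time. The last measure is then one of two values:

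- **Failure before month 3:** the baseline value, so the change is 0 at both three and six months. Entry requires a current DAS28-CRP of at most 3.5 (or DAS28-ESR of at most 3.8), so this is a fairly good score.
- **Failure between months 3 and 6:** the month-3 value, which may predate the loss of response.

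The Background section names the harm at issue: disease activity may rise in patients whose minimal effective dose is 1000 mg. If that happens, failures will be more frequent or more severe on 500 mg or 200 mg, and pre-flare scoring removes part of the difference the trial must be able to detect. An analysis described as conservative then becomes anti-conservative.

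The article also treats the same patients differently elsewhere. In the prediction analysis a responder must have a DAS28-CRP below 2.9 "at six months and no treatment failure) and non-responders (all other patients". A failed patient is a non-responder there whatever the score, yet may count as unchanged in the primary analysis.

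**Working it through.** **1. The plan's own figure.** Inputs: baseline SD 0.7, r = 0.17 in the most cautious row of Table 1, margin 0.6, two-sided alpha 0.05, power 95%, 2:1 allocation. For one comparison:

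N = 4.5 × (1.960 + 1.645)² × 0.7² × (1 − 0.17²) / 0.6² = 77.3

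The 1000 mg arm is 77.3/3 = 25.8, so 26, and the trial is 5 × 26 = 130, as printed. With r = 0.63, N = 48.0, giving 16 and 80, also as printed. (The table follows from a multiplier of 4.5 rather than the printed square of 4.5. That is a separate matter.) The calculation has no term for treatment failures, so it gives no failure rate to work from.

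**2. Size of the masking.** Let p_low and p_std be the failure proportions, F the flare size in DAS28 points, and c the share of failures with a DAS28-CRP recorded at the failure. If F and c are the same in both arms:

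hidden difference = (p_low − p_std) × F × (1 − c)

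None of these inputs is in the article. For an assumed 10-percentage-point excess and 1.5-point flare:

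- c = 0.8: 0.10 × 1.5 × 0.2 = 0.03, or 5% of the 0.6 margin
- c = 0.5: 0.10 × 1.5 × 0.5 = 0.075, or 12.5%
- c = 0: 0.10 × 1.5 × 1 = 0.15, or 25%
- c = 1: 0

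**3. Effect on the non-inferiority claim.** The planned ANCOVA was simulated with 28 versus 56 patients (140 split 1:2:2), baseline SD 0.7 and r = 0.63, with 10,000 trials per cell. A captured failure keeps its flare. An uncaptured one is scored as if no flare had occurred. Each scenario has a true difference of 0.6, so a claim is false and should occur in at most 2.5% of trials.

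| Failing, 1000 mg vs low dose | Flare | All captured | 80% | Half | None |
|---|---|---|---|---|---|
| 5% vs 35% | 2.0 | 1.5% | 5.7% | 32% | 99.7% |
| 5% vs 45% | 1.5 | 1.4% | 7.0% | 38% | 99.7% |
| 10% vs 40% | 2.0 | 1.5% | 5.6% | 29% | 99.7% |
| 10% vs 50% | 1.5 | 1.7% | 7.3% | 36% | 99.7% |

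With r = 0.17 the same four scenarios give 1.4–1.9%, 5.4–6.5%, 24–29% and about 96%.

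**4. A smaller true difference.** With 10% vs 30% failing, a 1.5-point flare and r = 0.63, the true difference is 0.20 × 1.5 = 0.30. Non-inferiority is claimed in about 33% of trials if every flare is scored, 48% at 80% capture, 76% at half, and over 99% if none is. A claim is not false here, since 0.30 lies inside the margin, but the estimated difference is still too small.

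**5. Equal failure rates.** With 10% in both arms and equal flares, the mean difference is not biased. The chance of a claim still rises, from 94.9% when flares are scored to 99.6% when none is (r = 0.63), because the spread due to flares is removed.

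**The case against.** The strongest reply is that a judgement of clear loss of response would ordinarily follow an assessment. If DAS28-CRP is recorded at that visit, the flare value is carried forward and later rescue cannot conceal the failure. The rule then works as a conservative one, and a transient flare could even count against the low dose. Failures found at the month-3 or month-6 visit are captured in the same way. Fig. 1, which could not be read, and the full protocol, published as supplementary material, may list the assessments for unscheduled visits.

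This stands as a limit on size. It does not remove the point: the article gives a scoring rule for the primary endpoint, and that rule as worded accepts any last value, including one from before the flare.

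Three stronger readings are tempting, and the document does not support them.

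- **Failures always vanish from the primary outcome.** They vanish only where the last DAS28-CRP predates the flare.
- **The intention-to-treat analysis offers no protection.** Carrying forward is spelled out for the per-protocol set only. The Interventions wording is general and may cover both sets, but intention-to-treat scoring is left open.
- **False claims in over 99% of trials.** This requires that no flare at all is recorded, in scenarios built so that the true difference equals the margin. It is an upper bound.

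Nor does the article show that failures will in fact be more frequent on the lower doses. It raises this as a possibility.

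**Conclusion.** The point holds in conditional form. The rule for treatment failures in the primary per-protocol analysis permits a baseline or month-3 value from before the flare to stand as the outcome. Bias in the mean difference towards non-inferiority needs two conditions: some failures without a DAS28-CRP at the failure, and more frequent or more severe failures in the ultra-low-dose arms. Failures before month 3 can affect all four primary tests; failures between months 3 and 6 affect the two six-month tests.

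The size cannot be derived from the article. Under the assumed inputs, the loss is small with good capture (5% of the margin for a 10-point excess at 80% capture) and serious with poor capture (false claims of 30–40% at half capture when the true difference equals the margin). Severity: should-fix, with medium confidence, because the full protocol may already secure the measurement.

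**What to change.** 1. Obtain a DAS28-CRP at the failure visit before the failure-defining treatment starts, and name it as the value used at all later time points. This concerns measurement only and changes nothing about who is treated or how.
2. Where no such value exists, do not carry forward baseline or month 3 as if the patient were unchanged. Use a prespecified unfavourable value, or an imputation that assumes worsening. At the least, make this a prespecified sensitivity analysis that must support the non-inferiority conclusion. The choice of value involves judgement, particularly for corticosteroids above 10 mg/day, which count as failure without a stated requirement for an RA flare. It should therefore be fixed before unblinding.
3. State that the same scoring applies in the per-protocol and intention-to-treat analyses.
4. Report failure rates by arm, and the share of failures with a DAS28-CRP at the failure.
5. An analysis of DAS28-CRP observed after rescue may be added only as a treatment-policy supplement, with the warning that rescue can itself mask inferiority.

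Cost: protocol or analysis-plan wording and one extra DAS28-CRP at an unscheduled visit. Non-inferiority becomes somewhat harder to claim when failures differ by arm.

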#### Assessments

At baseline, several characteristics of the patients will be measured, including demographics, disease and treatment characteristics. Also, possible predictors for response to ultra-low-dose RTX from peripheral blood will be collected, including (anti-)RTX drug levels and peripheral CD19 counts. Thereafter, visits will be performed at three and six months and when necessary in between (Fig. 1).

Several measures on disease activity will be collected during the study. The DAS28-CRP is a validated and widely accepted measure for RA disease activity and will be used as a primary outcome measure. It consists of four components: 28 tender joint count; 28 swollen joint count; CRP (mg/L); and patients VAS assessment of global disease activity (0–100) [26]. Remission is defined as DAS28-CRP < 2.4 and low disease activity by DAS28-CRP < 2.9 [32]. In addition, patient VAS assessment of pain, rheumatologist VAS assessment of global disease activity, acute phase reactants (CRP and ESR) and the OMERACT patient flare questionnaire are collected. To measure functioning of patients, the HAQ-DI, a validated instrument that is widely used in rheumatology is applied [33]. Quality of life is assessed using EQ5D-5 L, which is a validated instrument and comprises five questions and a visual analogue self-rating scale [34].

Adverse events are assessed at every visit during the study period and classified according to the Common Toxicity Criteria (CTC) [35]. In addition, we focus explicitly on infusion reactions and infectious events. Patients are asked to complete a short questionnaire after the RTX infusion on the occurrence of infusion-related adverse events. Medication use is charted using data from the electronic patient records on the use of DMARDs, corticosteroids and NSAIDs.

Costs will be calculated from a societal perspective. We will include the cost of outpatients’ clinic visits and telephone consultations, travel expenses for patients, costs of hospitalisation due to RA, costs due to health-related work absence and costs of medication during the six-month study period.

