The use of ultra-low RTX could present several advantages over standard low-dose RTX. First, infection risk should be lower, as RTX use is associated with a dose-dependent – although still low – risk of serious infection [17, 18]. Also, shorter infusion duration and less administered drug could lead to less patient burden and perhaps lower risk for infusion reaction [19]. Further, RTX treatment currently is relatively expensive, with costs for low-dose 1 × 1000 mg every six months being in the range of €4000–7000 per year. Although RTX was proven to be cost-effective in patients with an inadequate response to TNFi [20], use of ultra-low doses will further decrease costs and thereby improve cost-effectiveness. A combination of a possible effective dose of 200 mg every six months and expected price reductions due to upcoming availability of a rituximab biosimilar, could result in a bDMARD option availability for under €1000 per patient per year.

The use of an ultra-low dose of RTX might, however, also lead to increased disease activity in the subset of patients whose minimal effective RTX dose is 1000 mg. Therefore, prediction of response to ultra-low-dose RTX would be key to prevent patients from flaring experiencing accelerated joint damage [21]. Interesting baseline (at the moment of considering RTX retreatment) candidates for predicting the chance of good response on an ultra-low dose include higher RTX drug levels, absence of anti-RTX-antibody levels and low peripheral B-cell counts, as it might be hypothesised that these are all indicators for lower RTX need [22].

In conclusion, although the use of ultra-low doses of RTX seems promising, its effects have never been studied in a trial of proper design and size. We therefore aim to perform a RCT to study whether retreatment with one of two ultra-low RTX doses (1 × 200 mg or 1 × 500 mg) is non-inferior to retreatment with the standard low-dose RTX (1 × 1000 mg) for patients with RA who were already successfully treated with standard low-dose RTX. Also, we will analyse whether there are differences between retreatment with ultra-low dose and standard low dose in the occurrence of serious and non-serious adverse events and cost-effectiveness, and we will analyse whether (non-)response to (ultra-)low dose of RTX at six months can be predicted at the moment of initiating retreatment.

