### Objectives

The primary objective of the REDO trial is to compare the difference in efficacy between two ultra-low doses (1 × 200 mg and 1 × 500 mg) and standard low dose (1 × 1000 mg) of RTX retreatment on the change in DAS28-CRP, compared to a pre-specified non-inferiority margin of 0.6 DAS28 points, at three and six months. Therefore, the study has four primary endpoints. Although we are aware that patients are sometimes treated with longer intervals than six months, showing non-inferiority at six months is relevant, for ultra-low RTX dose with at least six-month intervals is still a lower cumulative dose as standard low-dose 1000 mg every 9–12 months.

The main secondary objectives are: to assess the difference in efficacy between the two ultra-low dose interventions for the same outcomes; to compare the proportion of patients with a DAS28-CRP < 2.9 (low disease activity), DAS28-CRP < 2.4 (remission) and remission according to Boolean ACR/EULAR criteria at three-month and six-month follow-up; to assess the between-group differences in the change in functioning (HAQ-DI) and quality of life (EQ5D-5 L); and to compare proportion (cumulative incidence and incidence density) of patients developing (treatment-related) adverse events in each study group over the duration of the study, with special attention to infusion-related adverse events and infections. Furthermore, the cost-effectiveness of both ultra-low RTX doses and the conventional low dose are compared for the six-month study period. For prediction modelling, baseline factors (including RF/ACPA status, CD19+ B-cell count, serum RTX, serum anti-RTX) will be tested for associations with the outcome of DAS28-CRP low disease activity state at six months.

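### The economic evaluation costs only RA admissions despite a societal perspective, and the carry-forward rule after treatment failure, read plainly, puts QALYs and costs on different post-failure courses.

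*Protocol article*

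**What the plan says.** **Costs.** The Assessments section states: "Costs will be calculated from a societal perspective". The list that follows covers outpatient visits, telephone consultations, patient travel, "costs of hospitalisation due to RA", and "costs due to health-related work absence and costs of medication during the six-month study period". The hospital item is tied to RA. The work-absence item is tied to health in general.

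**Expected harms.** The Background opens its list of advantages of ultra-low dosing with this: "First, infection risk should be lower, as RTX use is associated with a dose-dependent" risk of serious infection, a risk it also calls low. It adds a possible reduction in infusion reactions. The Objectives compare adverse events between arms "with special attention to infusion-related adverse events and infections".

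**After treatment failure.** Failure means an extra rituximab dose, a switch to another biological, or corticosteroids above 10 mg/day (Interventions). Patients then stay in the study, but "the last measure of disease activity and other outcomes will be used as outcome employing a" last-observation-carried-forward approach.

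**QALYs.** The closing paragraph of the statistical analysis section takes QALYs from EQ-5D-5L utilities. It expresses results as incremental net monetary benefit at EUR 20,000 to 80,000 per QALY, and does not say whether the carry-forward rule applies. The Objectives set the horizon at six months.

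**The concern.** There are two separate problems, and both sit in what the article states.

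1. A societal perspective is meant to count costs wherever they fall, yet inpatient care counts only if RA caused it. A patient admitted with a serious infection would contribute the lost work days but not the hospital bill. The trial follows these harms closely because they are expected to depend on dose, so the omitted cost may differ between arms. If infections are fewer on the lower doses, the omission works against those doses.

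2. Quality of life is a listed secondary outcome and EQ-5D is the instrument named for it, so a rule covering other outcomes reaches EQ-5D on a plain reading. Medication is counted over the whole six months, which includes an escape infusion. A failing patient would then be charged for rescue while the utility after rescue is replaced by an older value. Net monetary benefit would combine costs from one course with QALYs from another, in the patients whose costs change most.

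At stake is the cost-effectiveness comparison, a stated aim of a trial funded by two healthcare insurers. The primary endpoints are not affected.

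**Working it through.** The plan gives no figure for this point that could be reproduced. The sums below use its drug prices and willingness-to-pay range. Everything else is marked as an assumption.

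**Inputs from the article**
- Drug cost of 1 × 1000 mg every six months: EUR 4,000 to 7,000 per year (Background).
- Escape treatment named in the article: an extra 1 × 1000 mg (Interventions).
- Willingness to pay: EUR 20,000 to 80,000 per QALY (statistical analyses).
- Scheduled visits at three and six months, with others in between when necessary (Assessments).

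**Assumptions**
- Drug cost is proportional to dose.
- Failure occurs at month 3, and the carried EQ-5D differs from the true later value by 0.1 to 0.2.
- Failure rates differ by 10 percentage points between arms.
- Infection admissions differ by 0.5 to 5 percentage points, at EUR 3,000 to 10,000 each.

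**Step 1: drug money at stake**
- One 1000 mg infusion: 4,000/2 to 7,000/2 = EUR 2,000 to 3,500.
- Saving per patient with 500 mg: 0.5 × (2,000 to 3,500) = EUR 1,000 to 1,750.
- Saving per patient with 200 mg: 0.8 × (2,000 to 3,500) = EUR 1,600 to 2,800.
- One 1000 mg escape infusion therefore cancels the saving of 2,000/1,000 = 2 patients on 500 mg, or 2,000/1,600 = 1.25 patients on 200 mg. How failing patients are handled matters.

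**Step 2: QALY error per failing patient**
- Error held as a step over months 3 to 6: 0.25 × (0.1 to 0.2) = 0.025 to 0.05 QALY.
- Linear interpolation between visits, with only the month 6 value wrong: 0.125 × (0.1 to 0.2) = 0.0125 to 0.025 QALY.

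| Method | At EUR 20,000 per QALY | At EUR 80,000 per QALY |
|---|---|---|
| Step | EUR 500 to 1,000 | EUR 2,000 to 4,000 |
| Linear | EUR 250 to 500 | EUR 1,000 to 2,000 |

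The overall range is EUR 250 to 4,000 per failing patient.

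**Step 3: effect on the comparison**

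Bias per randomised patient = difference in failure rates × error per failing patient. At the assumed 10 points this is 0.10 × (250 to 4,000) = EUR 25 to 400, against a drug saving of EUR 1,000 to 2,800.

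**Step 4: direction, if failure is more frequent on ultra-low dose**
- Last EQ-5D taken during the flare and utility then recovers: QALYs are understated in the ultra-low-dose arm, which biases against it.
- Last EQ-5D predates the flare: the loss of utility is missed, which biases in favour of ultra-low dose.

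**Step 5: if other outcomes is read to freeze costs as well**

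The abstract lists costs among the secondary outcomes, so this reading is possible. The mismatch goes, but the escape infusion of EUR 2,000 to 3,500 is not counted. If every extra failure received one, 0.10 × (2,000 to 3,500) = EUR 200 to 350 per randomised patient would be missing. This is also wrong.

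**Step 6: unlisted infection admissions**

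The range is 0.005 × 3,000 = EUR 15 to 0.05 × 10,000 = EUR 500 per patient, small beside the drug saving.

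**The case against.** The strongest reply is that the article never says EQ-5D is frozen. The Interventions section does not name it. Where the analysis section restates the rule for the per-protocol set, it mentions disease activity only. The economic evaluation has its own paragraph, with no such rule. The full protocol is a supplement not seen here, and QALY derivation and the analysis population for an economic evaluation commonly belong there. **This stands in part:** the mismatch is an inference and the supplement may settle it. But the stated rule covers other outcomes without an exception, and both ways of reading it lead to a faulty calculation.

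On hospital costs, restricting admissions to the disease under study is a possible costing choice, and all-cause counting adds noise. This answers a demand for all-cause costing as the main analysis. It does not reconcile an RA-only list with a societal perspective when the omitted harms are expected to differ by dose.

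A reader might also draw three stronger conclusions that the documents do not support:
- *That the infection benefit is left out altogether.* Health-related work absence, visits, medication and EQ-5D can carry part of it, and infections are compared as a safety outcome. Only the inpatient cost is unlisted.
- *That infection admissions are the largest cost difference after drug price.* Nothing in the article ranks cost components. The Background puts infection first in a list and calls the risk low.
- *That the utility error is as large as the drug cost.* The error applies per failing patient and the drug saving to every patient. The error must be scaled by the difference in failure rates before the two are compared.

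**Conclusion.** The concern holds in two limited parts.

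**Stated in the text:** inpatient costs are limited to RA admissions under a declared societal perspective, so inpatient costs of treatment-related harms are omitted. On the assumed inputs this is EUR 15 to 500 per patient. If infections are fewer on lower doses, it works against those doses.

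**Inferred from the text:** the carry-forward rule, read plainly, freezes EQ-5D after failure while medication costs run on. The error is EUR 250 to 4,000 per failing patient, or EUR 25 to 400 per randomised patient at a 10-point difference in failures. Its direction is not fixed. The figures rest on assumed utility errors of 0.1 to 0.2 and on failure at month 3. Failure before the month 3 visit could lengthen the window and is not covered.

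Both parts should be corrected because cost-effectiveness is a stated aim, but they concern a secondary analysis only.

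**What to change.** 1. Extend the hospital item to admissions due to RA and to treatment-related adverse events, including infections and infusion reactions. Add all-cause admissions as a sensitivity analysis.
2. State in the economic paragraph that QALYs and costs use observed EQ-5D and observed costs for all randomised patients over the same six months, without carrying values forward at treatment failure.
3. If the full protocol already says this, bring the article's wording into line with it.

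**Cost.** Mostly wording: failing patients stay in the study and adverse events are assessed at every visit. The article does not say that the resource use needed to cost a non-RA admission is recorded, so a short item on admissions may have to be added. Rare, expensive admissions will widen the cost interval.
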